### Statistical evaluation

Using the G* Power software version 3.1.9.2, the calculus of power analysis was determined by choosing F tests for repeated measures, within-between interaction, since 3 groups will be studied, and each group will be measure before and after treatments. The effect size was determined using the formula [26]:$$ d=\frac{largest- smallest}{{\left(\frac{\sigma }{\sqrt{n}}\right)}^2} $$

The largest and smallest mean values, as well as the standard deviation were taken from the pilot clinical study [21]. The α error was set at 5% and the β error was set at 95%. The n value is the number of groups, i.e., three. According to the G* Power, a sample of 20 patients per group will be required for a power of 88.7%.

The profile of patients will be analyzed according to age, duration of disease, comorbidities and reported symptoms. A descriptive analysis will be conducted and presented by graph.

The clinical, histological, immunohistochemical, and spectroscopic findings will be submitted to inferential statistical analysis to verify the differences between the treatment groups. Associations between these results will also be analyzed. The significance chosen for the tests will be 95%.

First, the statistical distribution of the data will be evaluated. If the data conform to a Gaussian curve, parametric tests will be used. Graphs will be constructed in accordance with the means and standard deviations of the data.

However, if the data is unsuitable for a normal distribution, they will be analyzed with nonparametric tests. Box-type and quartile graphs, constructed according to the median of the results, will be used to present the data.

All data analysis will be performed using SPSS 22 Statistics software (IBM, USA).

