**Methods:**

The study is prospective, randomized and controlled, in a population of 60 women with histological diagnoses of VLS. There will be 3 treatments groups: PDT, PBM and topical corticosteroid (control group), where will be allocated by randomization 20 patients in each one. The clinical course will be monitored by measuring local temperature, itching, atrophy, and the area of the lesion. Histologically, the slides will be classified and will have the ordering of collagen fibers quantified. Immunohistochemical analysis will be done using the markers IFN-γ, TGF-β, CD4, CD8, IL-1, p53 and Ki-67. Finally, the spectroscopic evaluation will be done by reflectance. Descriptive and inferential statistical analyses will be conducted to compare the groups and make associations between different responses. The study is an open-label for patients with active symptomatic disease with a period of 1 year follow-up to determine the rate of recurrence in each groups.

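### The sample size paragraph sets β at 95% but reports 88.7% power (β = 11.3%); if a 95% power target was meant, 20 per group does not meet it by the article's own figure

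*Protocol article*

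**What the plan says.** The sample size paragraph is in the Statistical evaluation section of the protocol article. The calculation was made in G*Power for a repeated-measures design, with the test given as "choosing F tests for repeated measures, within-between interaction". It covers three groups, each measured twice, once before and once after treatment. The error rates follow: "The α error was set at 5% and the β error was set at 95" (per cent). The result is that "a sample of 20 patients per group will be required for a power of 88.7" (per cent). The abstract gives the same allocation for the three arms, "where will be allocated by randomization 20 patients in each one", or 60 in total.

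On the effect size, the section says "The largest and smallest mean values, as well as the standard deviation were taken from the pilot clinical study [21"] and, of the formula it prints, "The n value is the number of groups, i.e., three". It prints neither the means and standard deviation nor the resulting effect size, and it does not name the endpoint or the correlation between the two measurements.

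**The concern.** β is the probability of missing the effect that the trial is designed to find. A design that sets it at 95% accepts a 95% chance of failure, which nobody would intend. The same paragraph then reports a power that implies a quite different β. Changing the label from β to 1 − β does not settle the matter, because the paragraph would then set a target of 95% and report a sample that reaches 88.7%.

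The figure matters for how the results are read. The section on global benefits for the patients expects the light-based therapies to relieve pruritus as much as the corticosteroid does. A non-significant difference may therefore be taken as support for that expectation, and β tells the reader how often a real difference of the assumed size would be missed. The article should give that risk once, and correctly.

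**Working it through.** **Step 1: the definition.** Power = 1 − β.

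- β = 95% as written: power = 100% − 95% = 5%.
- Power = 88.7% as reported: β = 100% − 88.7% = 11.3%.
- If 95% was meant as 1 − β: β = 5%, and the shortfall is 95% − 88.7% = 6.3 percentage points.

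This needs only the two quoted sentences.

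**Step 2: can the 88.7% be reproduced?** Not from the article, because the effect size and the correlation between the two measurements (ρ) are not printed. The calculation below therefore takes 88.7% with 60 patients as given and solves for the effect that it implies.

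**Step 3: the effect implied by 88.7%.** Inputs from the article: k = 3 groups, m = 2 measurements (before and after), N = 60, α = 0.05, and an F test for the within-between interaction. Assumptions: no sphericity correction (exact with two measurements), and ρ varied from 0 to 0.9.

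- df1 = (k − 1)(m − 1) = 2 × 1 = 2
- df2 = (N − k)(m − 1) = 57 × 1 = 57
- Noncentrality: λ = f² · N · m / (1 − ρ)
- Power = probability that a noncentral F(df1, df2, λ) exceeds the upper 5% point of the central F(df1, df2)

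Power of 88.7% requires λ = 12.8. With ρ = 0.5 this is f = 0.231 (check: 0.231² × 60 × 2 / 0.5 = 12.8). The same λ corresponds to f = 0.327 at ρ = 0 and f = 0.103 at ρ = 0.9.

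**Step 4: the number needed for 95% power at that effect.** With f and ρ fixed, λ grows in proportion to N (12.805 / 60 = 0.2134 per patient).

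| Per group | Total N | λ | Power |
|---|---|---|---|
| 20 | 60 | 12.8 | 88.7% (by construction) |
| 25 | 75 | 16.0 | 94.9% |
| 26 | 78 | 16.6 | 95.7% |

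**Step 5: robustness.** The answer of 78 is the same for ρ = 0, 0.3, 0.5, 0.7 and 0.9, because only λ per patient matters. It is also unchanged if 88.7% is a rounding of anything from 88.65% to 88.75%. A plain one-way analysis of variance on three groups, calibrated in the same way, gives 78 too. Seen from the other side, 95% power with 60 patients at ρ = 0.5 would need f of about 0.261 instead of 0.231.

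**The case against.** The strongest reply is that this is loose wording. The same section gives the significance of the tests as 95%, another confusion of a probability with its complement, and the sentence that fixes the sample says clearly that 20 per group gives 88.7% power. On that view a reader knows what the design delivers. Much of this stands: the article states one β and one power, and the 5% and the 95% are two readings of the same misprinted figure. It does not remove the contradiction, because swapping β for 1 − β leaves a target that the reported power misses.

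A reader might go further in three directions, none of which the article supports.

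- **That the trial is too small and needs 26 per group.** No passage states a 95% power target; it is inferred from the slip. The 26 also rests on an 88.7% that cannot be verified.
- **That 60 patients is inadequate because no allowance is made for loss, or because the power depends on the second biopsy.** The article condenses a fuller protocol, where a loss allowance may be given, and it states no expected loss rate. The powered endpoint is not named. The pilot that supplied the means is described as assessing clinical response, itching, skin thickness and recurrence, so nothing ties the calculation to the biopsy.
- **That a null result could not be interpreted at all.** The misprint alone does not lead there, since the paragraph does give an operative power.

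**Conclusion.** The contradiction is real and certain by definition: β = 95% and power = 88.7% cannot both be true. If 95% was meant as the target power, the article's own figure puts 20 per group 6.3 percentage points below it. The corresponding 26 per group only illustrates the size of that gap. It assumes that 88.7% with 60 patients is correct and that the test is the one named, and it does not depend on ρ. It does not show that the design is deficient. This should be fixed, as an error in a stated operating characteristic that needs no change in sample size or conduct.

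**What to change.** Replace the sentence on error rates with one consistent statement: α = 5%, 20 per group, and power 88.7% (β = 11.3%) for the effect size actually used, with that effect size given as a number. Delete 95% as the value of β. If 95% power was the intended target, say plainly that 20 per group does not meet it. No sidedness should be attached to α, since the test is an omnibus F test.

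The 88.7% belongs only to the effect size that produced it. If that effect size is later revised, recompute the power and do not carry 88.7% over.

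The cost is a sentence or two of text. No extra patients are needed.

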### Randomization and dosimetry

A researcher not involved in the study will divide the patients into three groups by randomized order (Minitab 16, EUA). Then, opaque envelopes randomly containing information about application of photobiomodulation, photodynamic therapy or corticosteroid will be labelled with sequential numbers. The researcher responsible for treatments will open the first envelope and perform the procedure written therein. The internal contents will be revealed only after statistical analysis.

The dosimetry to be used in this study is based on a pilot clinical study performed by our group, which followed the recommendations from ASLMS [21]. In brief, the aim was to compare the effects of PBM and topical corticosteroid in VLS evaluating clinical response, itching, skin thickness (atrophy), and recurrence of disease after treatments. The study was prospective, randomized, and controlled in 20 women. CAAE number of Research Ethics Committee: 34,715,314.6.3001.0069. Corticosteroid group: clobetasol propionate 0.05% ointment applied once daily at a dose of 1 g/application for 4 weeks. PBM group: methylene blue 0.01% intralesional, laser λ = 660 nm, *P* = 100 mW, *I* = 510 mW/cm^2^, E = 4 J, exposure radiant = 20 J/cm^2^, *t* = 40 s, once a week for 4 weeks. The variation in intensity of itching was compared between groups, the corticosteroid group reduced the itching at 83.75%, and the PB group decreased 50.00%. The corticosteroid group showed significant variation in the skin thickness relative to PB (*p* = 0.006). This group had a reduction in thickness of the skin −27.51%, while in PB group showed an increase of 49.07%. The treatments were completed in December 2014 and until the month of September 2015 in the corticosteroid group there was 7 patients with no symptoms, while in the PB group there was 6 patients. In the corticosteroid group, the first recurrence was two months after the treatment, while the PBM was only 4 months later.

The groups to be studied and their dosimetry are showed at Table 1.

**Table 1 Tab1:** Characteristics of the groups

Group	Number	Treatment	Parameters
GC	20	Corticosteroid over the whole vulva	Clobetasol propionate 0.05% ointment applied once daily at a dose of 1 g/application (1 g sachets) for 4 weeks

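### The effect-size formula is not a standardised effect size and not the Cohen's f that the named test takes, so the stated 88.7% power does not follow from the stated method

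*Protocol article*

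**What the plan says.** The section Statistical evaluation of the protocol article describes a power calculation in G*Power made by "choosing F tests for repeated measures, within-between interaction", for three groups measured before and after treatment. The effect size is defined as

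d = (largest − smallest) / (σ/√n)²

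and the text adds: "The n value is the number of groups, i.e., three". The largest and smallest means and the standard deviation are said to come from the group's pilot study. The α error is 5%, and the β error is given as 95%. The conclusion is that "a sample of 20 patients per group will be required for a power of 88.7" per cent.

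The pilot is summarised under Randomization and dosimetry. It enrolled 20 women, and "the aim was to compare the effects of PBM and topical corticosteroid in VLS", so it had two arms. For itching, "the corticosteroid group reduced the itching at 83.75%, and the PB group decreased 50.00" per cent. No standard deviation is printed.

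**The concern.** A standardised effect size must be free of units, because the power of a given comparison cannot depend on whether itching is scored 0-10 or 0-100, or skin thickness recorded in millimetres or centimetres. The printed formula fails that test. It also puts the number of groups where a sample size would stand in a standard error, and it yields a quantity called d for a procedure whose input is Cohen's f.

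This calculation is the only justification in the article for 20 patients per group. The section Global benefits for the patients expects the photonic therapies to reduce pruritus as much as the corticosteroid. A non-significant difference could be read as bearing that out, and a quoted power near 89% would lend that reading weight that the calculation has not earned.

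**Working it through.** **1. What the formula equals.** With n = 3, (σ/√3)² = σ²/3, so d = 3Δ/σ², where Δ is largest minus smallest.

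**2. Unit dependence.** Multiplying the outcome by c multiplies Δ by c and σ² by c², so d is divided by c. Illustration with assumed values, Δ = 2 and σ = 2.5 on a 0-10 scale:

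| Scale | Δ | σ | 3Δ/σ² | Δ/σ |
|---|---|---|---|---|
| 0-10 | 2 | 2.5 | 6/6.25 = 0.96 | 0.80 |
| 0-100 | 20 | 25 | 60/625 = 0.096 | 0.80 |

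The patients and the data are the same, yet the effect size differs tenfold.

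**3. If the square is a misprint.** Δ/(σ/√3) = √3·Δ/σ. In the example this is 1.73 × 0.80 = 1.39 on both scales. It is free of units, but too large by √3 as a standardised difference, and still not f.

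**4. What the named test needs.** With two occasions, Cohen's f for the group-by-time interaction is

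f = SD of the group mean changes / (2σ),

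where the numerator is the population SD over the three groups. If R is the largest-minus-smallest change in SD units:

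- middle group at the midpoint: f = R·√(1/6)/2 = 0.204R
- middle group at one extreme: f = R·(√2/3)/2 = 0.236R

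So f is roughly a fifth to a quarter of R. A d cannot be entered in its place.

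**5. Can 88.7% be reproduced?** Not forwards: the article prints neither the means, the SD and the outcome that were used, nor the pre-post correlation ρ. Backwards, with N = 60, k = 3 groups, m = 2 occasions and α = 0.05:

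- degrees of freedom: (k−1)(m−1) = 2 and (N−k)(m−1) = 57
- noncentrality: λ = f²·N·m/(1−ρ) = 120f²/(1−ρ)
- power of 0.887 requires λ = 12.80, so f = √(12.80(1−ρ)/120)

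| ρ (assumed) | f | R = f/0.236 (middle group at an extreme) | R = f/0.204 (middle group at the midpoint) |
|---|---|---|---|
| 0.3 | 0.273 | 1.16 SD | 1.34 SD |
| 0.5 | 0.231 | 0.98 SD | 1.13 SD |
| 0.7 | 0.179 | 0.76 SD | 0.88 SD |

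The conventional f = 0.25 with ρ = 0.5 gives 93.2%, so that default does not explain 88.7% either. The figure fits only some undisclosed pair of f and ρ.

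**6. Sensitivity to the unit.** If 0.231 had been the value entered (ρ = 0.5), a change of unit that makes the printed formula ten times smaller would move the calculated power to 5.9%. One that makes it ten times larger would move it to practically 100%. The trial itself would be unchanged.

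**7. The β error.** A β of 95% would mean 5% power. If 95% was meant as the target power, it still differs from 88.7%.

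**The case against.** The strongest reply is that the inputs are out of sight. The formula is credited to a cited source and the means and SD to the pilot, and neither is at hand. The square may be a typesetting slip, and what was typed into G*Power is unknown. A condensed article may also leave the outcome and the correlation to the full protocol.

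Much of this stands. The absence of the outcome and of ρ is not itself held against the article. If the square is a slip, the units argument falls away. The rest does not: the sentence that sets n to three is plain prose, √3 remains in the ratio, and a d is still not the f that the test takes.

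A reader might go further and infer that the trial is underpowered. The document does not support that. Any figure for the real power needs an SD that is not printed, and the answer moves in either direction with the SD chosen. The printed pilot percentages can even point the other way. Suppose the formula had returned 0.231 (ρ = 0.5) from the itching gap of 83.75 − 50.00 = 33.75 points. Then σ = √(3 × 33.75/0.231) ≈ 21, and the difference is about 1.6 SD. For the thickness gap of 49.07 + 27.51 = 76.58 points, σ ≈ 32 and the difference is about 2.4 SD. Both exceed the 0.98 to 1.13 SD needed. These are assumptions too, since the article does not say which outcome or unit was used. They show only that the direction of the error is unknown.

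**Conclusion.** The point holds in this form: the printed effect size is 3Δ/σ², which is not a valid standardised effect and not the input of the named test, so 88.7% power for 20 per group does not follow from the stated method. That conclusion needs only the formula, the sentence defining n and the named procedure. It does not show that 20 per group is too few or too many.

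The size can be given only as a guide: at N = 60, power of 88.7% corresponds to a largest-smallest difference in change of roughly 0.8 to 1.3 SD over ρ from 0.3 to 0.7. This rests on the assumed ρ, equal groups of 20, no loss to follow-up and the usual repeated-measures model.

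The point deserves correction before the figure is relied on, because it concerns the only stated basis for the sample size.

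**What to change.** - Delete the formula and the sentence that sets n to the number of groups.
- Name the outcome that drives the size. Pruritus is the natural candidate, since the article makes it the recurrence criterion and the main complaint.
- Compute Cohen's f for the group-by-time interaction as the SD of the three group mean changes divided by twice the within-group SD. Give the means and the SD.
- State the mean assumed for the third group and its rationale, because a two-arm pilot cannot supply three group means.
- State the pre-post correlation, with a range if the pilot does not fix it.
- Keep N = 60 and report whatever power it gives for that f. The 88.7% should not be carried over unless it is what results. The table of f and R above can serve as a check.
- Correct the β error so that it agrees with the power reported.

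The cost is a recalculation and a few sentences. No patients, visits or analyses change. The restated power may come out higher or lower than 88.7%.

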#### Clinical

The temperature of the vulva will be measured with an infrared thermographic camera (C2, FLIR®, Nashua/NH, USA), which enables simultaneous measurement of the entire target area without physical contact. Measurements will be recorded as images in all sessions before, during, and after irradiation to observe the thermal fluctuation in the procedures.

In each session, the patients will be asked about the intensity of vulvar itching to assess its severity and duration, before and after irradiation, according to a visual analogical scale.

The vulvar skin clamping to evaluate the trophism will be done before irradiation at each session, using a digital caliper (Insize®, São Paulo/SP, Brazil), transversely and longitudinally in relation to the labia majora.

The area of the lesion will be monitored with a digital camera at every session (EOS Rebel T5, Canon®, Melville/NY, USA), before irradiation. To facilitate measurements, a metric scale will be placed on all vulvas for the photos. The areas of the lesions will be quantified using ImageJ software (National Institutes of Health, Maryland, USA).

The temperature, the intensity of itching, the clamping and the photographic images will be recorded for the patients of the GPDT and GPBM groups weekly for 30 days and for the GC group these measures will be done at first and 30th day.

If patients still report discomfort or undesirable symptoms from LEV after 30 days of treatment, they will continue with the same clinical protocol. If 60 days after the initiation of treatment they still remain symptomatic, the treatment that clinically appears to be better will be offered.

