#### Histological

The biopsies will be performed at two points: at baseline to confirm the VLS and subsequent inclusion in the research protocol, and at the end of 30 days to investigate the prognosis after treatment. The skin fragments will be placed immediately in vials containing 4% buffered formalin, identified with the patient’s numbers and names, in accordance with the standard routine of the hospital, and sent to the Pathology Laboratory at the Hospital Pérola Byington. There will be no mention of the study group on the vials, so the analysis will be performed blind by one experienced pathologist.

Three sets of histological sections will be processed. One set will be for staining in hematoxylin and eosin in order to recognize cells and their components and to make inferences on the histology of the tissue under an ordinary optical microscope. The slides of each patient will be classified and the classifications will be assigned scores so that they can be statistically analyzed.

Another set will not be stained and will be deparaffinized for analysis of the ordering of collagen fibers under a polarized light microscope, according to an already established protocol [25]. The third and final set of histological sections will be used for the immunohistochemical technique, which is described in the next subsection. It is emphasized that the method used in the analysis of collagen ordering will be quantitative, by measuring the optical birefringence (Δn) of the samples, in nanometers.

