### Global benefits for the patients

The criterion for recurrence will be pruritus, because it is the main patient complaint. The expected optical change in the skin is a reduction in reflection; lichen sclerosus leaves the skin depigmented, i.e. white, which is the color that most reflects. Therefore, as the symptoms diminish, we expect the skin to become less white, meaning that reflection also diminishes. We expect photonic therapies to decrease pruritus as much as the corticosteroid and, in addition, to not decrease the thickness of the skin, avoiding stenosis and pain.

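### At least 14 outcomes are tested between arms at one 5% level, none is named primary, and the 88.7% power is tied to no outcome

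*Protocol article*

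**What the plan says.** The Statistical evaluation section of the protocol article sends all four outcome domains to between-group testing: "The clinical, histological, immunohistochemical, and spectroscopic findings will be submitted to inferential statistical analysis to verify the differences between the treatment groups". One level is then given for every test: "The significance chosen for the tests will be 95" per cent, which can only mean a 5% level. Associations between the results are to be analysed as well.

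The variables are defined in the preceding sections:

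- **Clinical:** "The temperature, the intensity of itching, the clamping and the photographic images will be recorded", where the photographs yield the lesion area.
- **Histological:** a graded slide score ("The slides of each patient will be classified and the classifications will be assigned scores so that they can be statistically analyzed") and collagen ordering, obtained by "measuring the optical birefringence (Δn) of the samples, in nanometers".
- **Immunohistochemical:** seven markers.
- **In-vivo reflectance spectroscopy:** a relative reflectance percentage.

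The power calculation uses a repeated-measures within-between interaction F test with three groups and two measurements. It arrives at 20 patients per group and 88.7% power. The means and standard deviation come from the pilot study, but the variable they belong to is not given.

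The nearest thing to a lead outcome is in Global benefits for the patients: "The criterion for recurrence will be pruritus, because it is the main patient complaint". This selects pruritus as the definition of recurrence, not as the primary outcome.

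**The concern.** With no ranking, nothing in the article says which result decides whether the treatments differ. That matters here because the pilot outcomes point in opposite directions. In the pilot summary under Randomization and dosimetry, itch fell by 83.75% with corticosteroid and 50.00% in the comparison arm. Skin thickness fell by 27.51% with corticosteroid and rose by 49.07% in the comparison arm (p = 0.006). Which treatment looks better depends on which outcome leads.

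Two things are at stake. The chance of at least one false positive across the whole set of tests is well above the level of each single test. And the power figure cannot be set against any particular result when the trial reports.

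**Working it through.** **1. The plan's own figure.** The 88.7% cannot be reproduced, because the means, standard deviation, resulting effect size and within-patient correlation are not given. It can only be solved backwards. For the stated test, the noncentrality is λ = f² × N × m / (1 − ρ), with N = 60, m = 2, df1 = (3 − 1)(2 − 1) = 2 and df2 = (60 − 3)(2 − 1) = 57. Power of 88.7% at 5% needs λ of about 12.8:

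| Assumed within-patient correlation ρ | Effect size f needed |
|---|---|
| 0 | 0.327 |
| 0.3 | 0.273 |
| 0.5 | 0.231 |
| 0.7 | 0.179 |

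Check at ρ = 0.5: 0.231² × 120 / 0.5 = 12.8. The figure is attainable, but it cannot be checked for any variable. The same section also states "The α error was set at 5% and the β error was set at 95" per cent, which does not fit a power of 88.7%. That is a separate slip and does not enter below.

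**2. The count.** Temperature, itch, clamping and lesion area (4), slide score and birefringence (2), seven markers (7) and reflectance (1): 4 + 2 + 7 + 1 = 14. This is a minimum. Clamping is measured "transversely and longitudinally in relation to the labia majora", so it could count twice. Reflectance could be tested at several wavelengths. Twelve-month recurrence and the tests of association come on top.

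**3. Independent outcomes, no true difference on any.** One three-group test per outcome at 5%:

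- 14 outcomes: 1 − 0.95^14 = 0.512, with 14 × 0.05 = 0.7 false positives expected.
- 15 outcomes (adding recurrence): 1 − 0.95^15 = 0.537.
- Four clinical outcomes alone: 1 − 0.95^4 = 0.185.
- Clinical plus histological: 1 − 0.95^6 = 0.265.

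**4. Correlated outcomes.** The documents give no correlations, so these are assumed. Simulation under no true difference used three arms of 20, normal data, equal correlation between the 14 outcomes and one three-group F test each:

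| Assumed correlation between outcomes | Chance of at least one significant test |
|---|---|
| 0 | 51% |
| 0.2 | 47% |
| 0.3 | 44 to 45% |
| 0.5 | 35 to 37% |
| 0.7 | 27% |

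Ranges show the spread between repeated simulations.

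**5. Cost of Holm adjustment over two comparisons.** The smaller p-value is tested at 5%/2 = 2.5%, the larger at 5%. Pairwise power comes from the noncentral t distribution with noncentrality d × √(20/2) and 57 degrees of freedom (variance pooled over three arms). The documents give no standardised difference, so d is assumed:

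| Assumed difference d (SD) | Power at 5% | Power at 2.5% |
|---|---|---|
| 0.8 | 70% | 59% |
| 0.98 | 86% | 78% |
| 1.2 | 96% | 93% |

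**The case against.** The strongest reply is that most of the 14 outcomes are not efficacy claims. The Discussion presents the markers and biopsies as a way to understand mechanism, and says that a spectral difference would lead to a further study. On that reading the relevant family is the four clinical outcomes, and the figure is about 19%. This stands as a limit on the size. It does not remove the point, because the Statistical evaluation section treats all four domains alike and calls none of them exploratory.

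A second reply is that a multiplicity procedure may sit in an analysis plan that is not shown. That is fair for the procedure. The primary outcome and the variable behind the sample size are not normally left there, and this article gives the software version, test family and effect-size formula without naming the variable.

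Three stronger readings are tempting and not supported:

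- A reader might infer that the trial misstates its family-wise error as 5%. The article states no family-wise error, only a level for the tests and an alpha for the power calculation.
- A reader might infer unadjusted pairwise testing of the three arms, which would raise the 14-outcome figure to between 50% and 84% for assumed correlations from 0.7 down to 0. The article specifies no pairwise tests and does not say whether any would be adjusted.
- A reader might infer that any single significant result is enough for a claim. No such rule is written. What is missing is a statement of which result counts.

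**Conclusion.** The concern holds in limited form. The article fixes one 5% level for at least 14 between-group outcomes, names no primary outcome, and gives a power figure that belongs to no stated variable. The chance of at least one false positive is 51% under independence and about 45% and 35% at assumed correlations of 0.3 and 0.5. All of these assume one three-group test per outcome and no true difference on any outcome. Independence is doubtful for markers taken from the same biopsy, and the pilot thickness result sits uneasily with no difference anywhere, so one half is not a prediction for this trial. Restricted to the four clinical outcomes, the figure is about 19% if they are independent.

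**What to change.** Before data are analysed:

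1. Name one primary outcome: the pilot variable actually used for the power calculation, as day-30 change in itch or in skin thickness. State the effect size, standard deviation and power for that variable.
2. Make PDT versus corticosteroid and PBM versus corticosteroid its two confirmatory comparisons, with Holm adjustment.
3. Label all other outcomes exploratory and report nominal p-values.
4. Do not make the thickness test conditional on a significant itch difference. Global benefits for the patients expects the light therapies to relieve itch to the same degree as corticosteroid while sparing skin thickness. If itch is truly equal, a Holm-adjusted itch gate would open at most 5% of the time.
5. Report the itch differences with confidence intervals, and do not read a non-significant itch test as showing similarity to corticosteroid.

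The changes are mainly wording and need no extra patients as long as the primary claim is one of difference. A confirmatory claim of similar itch relief would be another matter, since it needs a non-inferiority margin and its own sample size. The price is some pairwise power, about 86% to 78% for the smaller p-value under an assumed 0.98 SD difference. The remaining outcomes can also no longer support confirmatory claims.
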